4.5 Exclusion criteria

Individuals who meet one of the following criteria will not be enrolled in the clinical trial:

There is limited blood clotting (Quick < 50%, PTT > 50 sec., platelet count > 50/nl)

There is an extrahepatic bile duct carcinoma of the Klatskin type in stage bismuth 2-4 or an intrahepatic bile duct carcinoma

The malignant underlying disease is operable or can be cured by chemotherapy (e.g. aggressive non-Hodgkin's lymphoma)

The patient is pregnant or breastfeeding

The patient participates in another interventional study on EUCD or PTBD

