6.1 Screening visit

A paper-bound explanation of the study (own form) for the intervention (commercial form) and the sedation or anaesthesia (commercial form) of the patient is provided. Each potential study patient will receive a CT or MRI abdomen in addition to an abdominal sonography. The inclusion and exclusion criteria are checked (Case Report Form , p.2). Every patient who has been positively screened is included in the study if written consent is obtained (Case Report Form, p. 1). In the case of patients who are still capable of giving birth, a possible pregnancy is excluded by pregnancy tests.

It is assumed that almost all positively "screened" patients want to undergo an intervention under study conditions. In this situation, surgery is usually either not possible (pre-operated abdomen, advanced tumour disease) or is associated with a considerable risk. The performance of a PTBD/EUCD is therefore mostly without alternative. The screening list lists (separate form) which patients have been screened positively (inclusion and exclusion criteria fulfilled). Should a patient not be included in the study (e.g. because of refusal to participate in the study), this is briefly explained.

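### The platelet limit in the clotting exclusion of Protocol section 4.5 is reversed: it reads above 50/nl where below 50/nl is required

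*Protocol*

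**What the plan says.** Section 4.5 of the protocol opens its list with "Individuals who meet one of the following criteria will not be enrolled in the clinical trial". The first item on that list is "There is limited blood clotting (Quick < 50%, PTT > 50 sec., platelet count > 50/nl". The bracket does not say whether one of the three limits is enough or all three must be met.

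Section 6.1 makes the list operative at screening: "The inclusion and exclusion criteria are checked (Case Report Form , p.2". Section 10.1 says that the CRFs are developed from the protocol.

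No other section states a platelet threshold. The baseline data listed in section 6.2 include bilirubin but no platelet count, and section 5.6 says that concomitant diseases are not documented.

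**The concern.** The three limits are meant to specify one condition, and two of them do. The third points the opposite way. Followed literally, it turns away patients with adequate platelets and does nothing to keep out patients with low counts whose Quick and PTT pass.

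What is at stake is a safety criterion. Both arms puncture the bile duct: through the stomach or intestinal wall in EUCD (section 1.1) and through the liver in PTBD (section 5.1). Section 8.1 lists bleeding or haematoma and haemobilia among the complications to be recorded. This is the only clotting exclusion in the trial. Because neither platelet counts nor concomitant diseases are among the listed data items, a misapplied limit would be hard to detect afterwards.

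**Working it through.** No plan figure has to be reproduced; the question is the direction of one inequality. It can be settled from the sentence itself and the basic meaning of the three tests.

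**Step 1. Compare each limit with the lead phrase.** The lead phrase is "There is limited blood clotting".

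| Limit in section 4.5 | What a value meeting it means | Agrees with the lead phrase? |
| --- | --- | --- |
| Quick < 50% | low value, clotting impaired | yes |
| PTT > 50 sec. | prolonged time, clotting impaired | yes |
| Platelets > 50/nl | count above the threshold, not impaired on this test | no |

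**Step 2. Look for a correction elsewhere.** There is none: "platelet count > 50/nl" is the only platelet limit in the protocol.

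**Step 3. Apply the bracket literally.** The patient values below are assumed for illustration. T means that the limit is met and F that it is not, in the order Quick, PTT, platelets.

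| Patient (Quick %, PTT sec., platelets/nl) | As written | With < 50/nl |
| --- | --- | --- |
| A: 90, 30, 200 | F, F, T | F, F, F |
| B: 90, 30, 30 | F, F, F | F, F, T |
| C: 40, 60, 30 | T, T, F | T, T, T |

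*If any one limit suffices:*
- A is excluded as written (F or F or T) and would not be excluded after correction.
- B is not excluded as written (F or F or F) and would be after correction.
- C is excluded either way.

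*If all three limits must be met:*
- C, abnormal on every test, is not excluded as written (T and T and F) and would be after correction.
- A and B are not excluded either way.

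So the bracket gives a wrong result under both readings. Taken on its own terms, it never lets a count below 50/nl contribute to exclusion. Reversing the sign removes the contradiction under both.

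**The case against.** The strongest reply is that the error reveals itself. The lead phrase governs the bracket, and no clinician would call 200/nl impaired clotting or overlook 30/nl. On the any-one reading, the literal text would bar patients with normal counts, so recruiting the 212 patients in section 4.1 would be unworkable and the slip would surface at the first screening. The English shows other signs of translation; section 6.2, for instance, names the wrong anatomical structure for a difficult ERCP. The CRF is not at hand, so nobody can say that centres worked with the reversed sign.

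The exclusion also decides who enters the study, not who is punctured. Each centre performs its default procedure (section 4.2), the protocol claims no risk beyond that of the procedure itself (sections 1.3 and 5.2), and section 6.1 says that most of these patients have no real alternative. Nothing in the analysis changes.

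Most of this stands. The slip is probably clerical, the intended direction is plain, and neither harm to a patient nor a bias in the results is shown. It limits the likely practical effect but does not make the sentence right. A centre that follows the text applies the safety limit backwards, and a centre that reads it sensibly departs from the written criterion. A damaged inequality sign in the PDF text is unlikely, because the two other signs in the same bracket are in the expected direction.

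**Conclusion.** The platelet limit is wrong as written: one of three limits in an operative safety exclusion is reversed. The conclusion rests only on the wording of section 4.5, the usual meaning of the three tests, and the absence of any other platelet limit in the protocol. The illustrative patient values show the logic and carry no weight beyond that.

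The protocol gives no platelet data, so the number of patients affected cannot be estimated. There is no claimed effect on the sample size, the primary non-inferiority test, the ITT or PP sets, or the comparison of complications. The correction is needed because a safety threshold is stated backwards, and for that reason alone.

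**What to change.** In section 4.5, change the platelet limit from > 50/nl to < 50/nl, with the clinical leads confirming that 50/nl is the intended threshold. Check that the eligibility page of the CRF (page 2) carries the same sign, and notify all centres of the correction.

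The cost is a one-character amendment, one check of a form and one letter to the centres. Sample size and analysis stay as they are.

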4.6 Termination criteria

4.6.1 Premature discontinuation of individual patients

Every patient has the right to withdraw his or her consent to participate in this clinical trial at any time without giving reasons. If possible, the time and reason for the termination of the study should be noted in the CRF. Data collected until then will also be noted in the CRF.

Reasons for the premature termination of the study may be

- withdrawal of consent by the patient.

- Study participants can no longer be contacted.

4.6.2 Premature termination of the trial or closure of a centre

In the event of an accumulation of serious adverse events (SUEs) (see Chapter 8.2) in a trial site or trial arm (PTBD or EUCD), the Steering Committee is involved. The Steering Committee reserves the right to draw the appropriate consequences from the reports received, such as the closure of a trial site or termination of the study.

A serious adverse event (SUE) is any adverse event that occurs during the course of the study, regardless of the link to the intervention, and has one of the following consequences for the patient

- Death

- Unplanned surgical intervention necessary

- Permanent damage or permanent disability remains

- Unscheduled return to hospital or extended hospital stay: > 10 days

- Unplanned stay intensive care unit: > 1 night

All investigators involved must be informed immediately of any stop or interruption of the trial. The decision is binding on all trial centres and investigators.

If the clinical trial is terminated prematurely, all study materials (completed, partially completed) must be returned to Data Management.

**5. TREATMENTS/ INTERVENTIONS**

5.1 Description of the treatment(s)/ intervention(s)

PTBD

PTBD is performed in the first step by means of (colour contrast Doppler) ultrasound-guided puncture of an (dilated) intrahepatic bile duct using an access needle (e.g. Chiba needle (22G/0.7mm diameter). In the next step, the application of contrast medium into the bile duct system is performed under radiological fluoroscopy. The access route should be at a sufficient safety distance from neighbouring structures, i.e. the pleura in case of right-sided access.

Ideally, after KM filling of the bile duct system, a wire should be advanced distally beyond the stenosis in the common bile duct. This can also be done after changing to a larger wire (from 0.018" to 0.035"). After placement of an appropriate guide wire, a corresponding metal stenosis implantation (SEMS) should be performed in the same session in the area of the stenosis of the common bile duct (usually 8 or 10 mm diameter with different lengths (usually 6 -10 cm).

For further precision, the release of the metal stent can (not obligatory) be controlled by an additional luminal endoscopic visualization. (usually in relation to the papilla or the protrusion into the duodenum). This is particularly relevant with regard to endoscopic reintervention. Even in cases of tumour-related duodenal stenosis (use of a thinner endoscope) or altered anatomy after abdominal surgery (e.g. access via the feeding loop after Billroth II surgery). it is very often possible to reach the papilla (e.g. using a gastroscope).

Leaving a percutaneous plastic drainage after successful implantation of a metal stent should be avoided (counted as reintervention). If metal stent implantation is not possible in the initial PTBD, an internal/external plastic drainage should be inserted and the sole external drainage should be avoided (highest risk of complications).

EUCD

Endosonographically controlled cholangiodrainage (EUCD) is performed according to the current state of knowledge of this technique (2-9,14,15).

The choice of the respective EUCD method depends on the examiner. First and foremost, however, an antegrade stenting in the sense of an EUS-AD (wire is passed over the stenosis) should be performed.

should be attempted, since - in contrast to the transluminal procedure - the original anatomy of the bile duct system is preserved and the least complications are expected.

In the event of unsuccessful wire advancement via the tumor stenosis in the context of an intended EUS-AD, the next step should be an EUS-guided transhepatic drainage (EUS-HD) with metal stent implantation or EUS-guided choledochal drainage (EUS-CD) with metal stent implantation. The respective access route - transesophageal, transgastral, transduodenal or transenteral - depends on the disease or anatomy (e.g. in the case of Roux Y anastomosis transenteral). In the evaluation of this study, the respective, access-path dependent interventions are subsumed under the designations of an EUS-HD or an EUS-CD.

EUS-guided interventions such as the EUS-guided rendezvous procedure, EUS-guided cholecystomy or EUS-guided jejunostomy, which is used e.g. in afferent loop syndrome and usually requires the use of a lumen apposing metal stent (LAMS), are not the subject of this study.

5.2 Risks of the study intervention

The study does not pose any additional risk for the patient in addition to the usual risks of the respective intervention.

5.3 Randomisation and blinding

Randomisation is not carried out, as one centre cannot usually offer both interventions (PTBD and EUCD) of the same high quality due to the complexity and experience required. Therefore, each centre offers the respective standard method (EUCD or PTBD). At least 10 study centres will participate in the study. When selecting the centres, care is taken to ensure that both university hospitals and non-university institutions are selected for both groups. All potentially eligible patients will be screened (see Chapter 6.1) and, if suitable, informed about the study. It is assumed that the recruited patients of both groups have similar characteristics and are comparable. Possible differences in patient characteristics are taken into account in the data evaluation. However, it is not expected that different patient characteristics (e.g. pancreatic carcinoma and bile duct obstruction versus LK metastasis in liver hilus with bile duct obstruction) will have a relevant influence on the success or failure of the intervention.

Due to the nature of the interventions, the attending physician cannot be blinded. Since only one of the two surgical techniques is used in a centre, the patient and study nurses cannot be blinded either. With the exception of the secondary endpoint of pain perception, the endpoints, especially the primary endpoint, are objectively measurable outcomes. Therefore, it is assumed here that there is little room for influence and that the risk of bias is low. The biometrician has no access to the data until after the database has been closed.

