5. A portal vein-oriented puncture of a peripheral bile duct is particularly helpful if the intrahepatic bile ducts are hardly congested (13).

The same applies to EUCD. For this, the best method and the best devices (e.g. in the choice of the metal stent) according to the current state of knowledge should be used (14). As already mentioned, various procedures are available here (transluminal stenting, antegrade stenting while retaining the existing bile duct anatomy and the rendezvous procedure with conventional ERCP). In a recent publication by Tyberg and colleagues, an algorithm was proposed to determine how the respective method should be applied depending on the dilatation of the intrahepatic bile ducts (dilated versus non-dilated) and the success of the rendezvous procedure or the success of an antegrade stenting can take place (in the next step then transluminal, e.g. as EUS-HGS or EUS- CDC) (15). Most of the studies conducted so far have only selectively chosen one of the different procedures of EUCD as a comparative method to PTBD, which could have led to a selection bias.

In contrast, the planned study will compare the three main techniques of EUCD, i.e. antegrade drainage, transhepatic drainage and drainage into the D. common bile duct, with PTBD and its optimizations described above. The specifications for the EUCD were coordinated with a recognized expert in the field of EUCD ([name], Gera). The study will be conducted prospectively, multicentre and non-randomized (reason for non-randomization: each centre offers the technique that it masters best).

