6.2 Baseline visit

Facts of the clinical picture are documented (Case Report Form,p.3) . Cause of malignant bile duct obstruction, date of first diagnosis of the malignant underlying disease, cause of unsuccessful or for anatomical reasons not feasible ERCP.

The bilirubin value in mg/dl as an expression of the bile duct obstruction or cholestasis is measured and noted. The baseline visit should be performed the day before the intervention. Depending on the timing within the centre, baseline visit can be on the same day as screening visit if the intervention is scheduled for the following day.

Data that are documented as part of the study:

Demographics

- Gender

- Age

- Size

- Weight

Cause of the malignant bile duct obstruction (no multiple answers)

- Pancreatic carcinoma

- Distal bile duct carcinoma or extrahepatic bile duct carcinoma (Bismuth I)

- Gall bladder carcinoma

- Stomach cancer

- Duodenal carcinoma

- Papillary carcinoma

- Metastasis of another malign disease

- Other cause

Date of first diagnosis of the underlying malignant disease

Cause of unsuccessful or for anatomical reasons not feasible ERCP (no multiple answers)

- Gastric outlet stenosis/duodenal stenosis (tumour-related or benign cause)

- Difficult to probe the optic disc using ERCP

- For (partial) gastrectomy

- Biliodigestive anastomosis

- Following bariatric surgery

- Other cause

Laboratory chemical result of bilirubin determination (in g/dl) Pain intensity on the visual analogue scale (0-10)

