9.2 Statistical evaluation

The primary endpoint is the technical success rate in malignant distal choledochial stenosis using a self-expanding metal stent. The non-inferiority of PTBD compared to EUCD shall be demonstrated. The corresponding test hypothesis is

H0: pEUCD - pPTBD ≥ δ vs. H1: pEUCD - pPTBD < δ

Where pPTBD describes the technical success rate in the EUCD group, pPTBD the technical success rate in the PTBD group and δ=0.1 the non-inferiority limit.

The non-inferiority of PTBD to EUCD is verified by the Farrington/Manning test with a one-sided significance level of 2.5%.

Since this is a non-inferiority study, the primary evaluation will be based on both the Intention-To-Treat (ITT) Set and the Per-Protocol (PP) Set. In the ITT set, all patients are considered in whom the intervention was performed, even if it was technically unsuccessful or participation in the study was terminated prematurely. If the intervention has to be terminated prematurely (e.g. due to organ perforation), this patient is included in the primary evaluation. The primary evaluation is based on the assumption of technical failure in these patients.

In the PP Set, only those patients are included in the evaluation for whom the intervention was performed and the technical success was measured.

In sensitivity analyses, best case and worst case scenarios are calculated for the missing values. In addition, regression models are planned to investigate the influence of confounders on the endpoints. The variables intervention (EUCD with subgroups or PTBD with side localisation), BMI or bilirubin value are considered as input variables in the baseline study. The binary outcome variable is the technical success of the intervention. The affiliation of the individual patients to the two evaluation collectives is defined in SAP before the database is closed.

If non-inferiority can be shown with regard to the technical success rate, the occurrence of at least one complication (expected complication rate for both interventions: 10-20%) is compared hierarchically in the next step and tested for differences between the groups (based on the ITT set). Due to the hierarchical approach, the full level alpha, in this case two-sided 5%, is tested.

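### Bile-duct dilatation, which section 1.1 ties to technique in both arms, is neither recorded nor a regression input, so the listed data cannot show or adjust for a difference between centre-based arms

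*Protocol*

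**What the plan says.** Section 5.3 assigns each centre the one technique that is standard there, assumes that the two groups are comparable, and states that any differences in patient characteristics will be allowed for in the evaluation. The next sentence says "it is not expected that different patient characteristics", with tumour type as the example, will have a relevant influence on whether the intervention succeeds.

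Section 1.1 mentions duct dilatation for both techniques. For PTBD, a portal-vein-oriented puncture "is particularly helpful if the intrahepatic bile ducts are hardly congested". For EUCD, it reports a published algorithm in which the method "should be applied depending on the dilatation of the intrahepatic bile ducts (dilated versus non-dilated". Section 5.1 takes up that publication as one item in a list of references.

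Section 6.1 provides the imaging: "Each potential study patient will receive a CT or MRI abdomen in addition to an abdominal sonography".

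The list in 6.2 introduced by "Data that are documented as part of the study" covers sex, age, height, weight, cause of obstruction, date of diagnosis, reason for ERCP failure, bilirubin and pain. The list in 6.3 covers times, stent details, technical success, PTBD localisation and EUCD technique. Neither contains duct calibre or dilatation, and chapter 7 refers back to chapter 6 for what is collected. For the regression of technical success, section 9.2 names the intervention (with EUCD subgroups or PTBD side) and then says "BMI or bilirubin value are considered as input variables in the baseline study".

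**The concern.** Without randomisation, measured baseline variables are the only means of checking whether the two sets of hospitals treated similar patients. The protocol gives a technical reason why dilated and non-dilated ducts are approached differently, and the inclusion criteria in 4.4 do not require dilated ducts, so the factor can vary between hospitals. If it also affects success, a difference in case mix shifts the crude success rates even when the techniques perform equally. The shift can hide non-inferiority or suggest it wrongly, depending on which arm has the harder cases.

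This is not a detail that can wait for the SAP. An SAP chooses analyses of the data collected and cannot adjust for a variable outside them. For this factor, the undertaking in 5.3 cannot be met from the listed data.

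**Working it through.** **The plan's own figure.** Inputs from 9.1: success 0.95 in both arms, margin 0.10, one-sided 2.5%, power 80%, drop-out 5%. The Farrington/Manning restricted estimates under the null are 0.870 (PTBD) and 0.970 (EUCD).
- Null SD term: √(0.870×0.130 + 0.970×0.030) ≈ 0.376
- Alternative SD term: √(2×0.95×0.05) ≈ 0.308
- n = [(1.960×0.376 + 0.842×0.308)/0.10]² ≈ 99.4, so 100 per group
- 100/0.95 = 105.3, so 106 per group

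Both figures match the protocol. Exact enumeration at 106 per arm gives power 0.847 at 95%/95% and type I error 0.023 at 95%/85%. No stated number is in dispute.

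**Illustration of confounding.** The documents give neither the share of non-dilated ducts nor its effect on success, so everything below is assumed. With equal techniques:

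crude gap = (PTBD share non-dilated − EUCD share non-dilated) × (success dilated − success non-dilated)

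For example, at 97%/80% with shares of 10% (EUCD) and 30% (PTBD), the gap is 0.20×0.17 = 0.034. EUCD success is 0.9×0.97 + 0.1×0.80 = 0.953 and PTBD success is 0.7×0.97 + 0.3×0.80 = 0.919. P(NI) is the probability that the test shows non-inferiority, by exact binomial enumeration at 106 per arm. Shares are EUCD vs PTBD.

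| Success dilated / non-dilated | Gap, 10% vs 30% | P(NI), 10% vs 30% | P(NI), 20% in both | Gap, 10% vs 15% | P(NI), 10% vs 15% | P(NI), 12.5% in both |
|---|---|---|---|---|---|---|
| 97 / 80 | 3.4 points | 0.42 | 0.78 | 0.85 points | 0.77 | 0.84 |
| 97 / 85 | 2.4 points | 0.58 | 0.83 | 0.6 points | 0.82 | 0.87 |
| 96 / 88 | 1.6 points | 0.66 | 0.82 | 0.4 points | 0.81 | 0.85 |

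The 20% reference has the same average share as the 10% vs 30% case. The matching reference for 10% vs 15% is 12.5% in both arms. Against the matching reference, the large imbalance costs about 16 to 36 percentage points of power and the small one about 3 to 8 (0.033 to 0.075 unrounded).

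**Opposite direction.** Let PTBD be truly 10 points worse in each stratum, with the harder cases in the EUCD arm. At 30% (EUCD) vs 10% (PTBD), false non-inferiority is 0.115, 0.079 and 0.055 for the three rows. At 10% vs 5% it is 0.037, 0.032 and 0.029. With 20% in both arms it is about 0.024–0.025.

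**Room for adjustment.** At 95% success, 200 evaluable patients yield 0.05×200 = 10 expected failures.

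**The case against.** Four points on the other side have weight.

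First, a reader might infer that the protocol makes dilatation the determinant of the EUCD route. It does not. The algorithm is background, taken up by citation only. The operative rules in 5.1 leave the method to the examiner, with antegrade stenting first, and make the access route a matter of disease or anatomy.

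Second, a reader might infer that dilatation is a main driver of technical success. No section says so. Calling a puncture technique helpful in hardly congested ducts is advice on technique and does not report a lower success rate. The sentence in 5.3 also uses tumour type, not duct calibre, as its example.

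Third, the illustration depends on the assumed imbalance. A 30% non-dilated share may be high in patients with clinically relevant stenosis and raised bilirubin, and 7.2.1 describes success for two EUCD methods by outflow into dilated ducts. At 10% versus 15% the effect is small.

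Fourth, the information is not irretrievably lost. Imaging is required and source data are archived, so duct status could be abstracted later. Bilirubin is recorded as an expression of obstruction. However, later abstraction would be unplanned and might be done with outcomes known, and bilirubin does not measure duct calibre.

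These points limit the claim. They do not supply the missing variable.

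**Conclusion.** The point holds as a gap between an undertaking and the data listed to honour it: section 5.3 says differences will be taken into account, section 1.1 identifies a technically relevant one, and sections 6.2, 6.3 and 9.2 leave it out.

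It does not follow that the comparison is biased, or that the primary result will be wrong. That would need an effect on success and an imbalance between arms, and the documents give neither. Under the assumed success rates, the consequence ranges from slight (10% versus 15%) to serious (10% versus 30%, with P(NI) of 0.42–0.66 under equal techniques). Neither the direction nor the place in that range can be known from the protocol.

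The overview figure in chapter 6 and the CRF are not available. Since chapter 7 refers to chapter 6 for the parameters and 10.1 ties the CRF to the protocol, an unlisted field is unlikely but cannot be excluded.

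**What to change.** - Add to the baseline CRF, read before the intervention from the sonography and CT or MRI already required: intrahepatic ducts dilated (yes/no), and the intrahepatic and common bile duct diameters in mm.
- Tabulate these by arm.
- Include one dilatation variable in the regression of technical success planned in 9.2 as a supportive analysis. Keep the model sparse or penalised, because only about 10 failures are expected.
- Qualify the sentence in 5.3 so that it no longer implies that no patient characteristic is expected to matter.

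The cost is two or three CRF fields, one table, one model term and one sentence, with no new examination and no extra patients. The adjusted estimate will be imprecise. The primary Farrington/Manning test remains unadjusted, so its error rates under imbalance do not change. The gain is a visible check of comparability and a supportive adjusted estimate.
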